#### Misoprostol

The iNCK contains three 200 μg dissolvable misoprostol tablets. Mothers will be instructed to take the three tablets immediately after delivery of the baby and before delivery of the placenta to reduce the risk of PPH. For participants who deliver via C-section, the decision on misoprostol use will be deferred to the attending clinician. Data collectors will retrieve any unused misoprostol tablets from families at the home visit on day 29. Due to its low cost, oral route of administration, and no requirement for cold-chain storage, misoprostol can be used in low-income and remote settings and has been shown to be safe [21, 22].

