#### Sunflower oil emollient

The mother/caregiver will be directed to massage a small amount of sunflower oil (Synergy Crafts, Karachi) onto the baby's skin all over their body, avoiding the face and scalp, once per day, from the day of birth until day 28 of life. In low-income countries, sunflower oil has been proven to be effective in preventing hospital-acquired infections in preterm neonates and supporting their critically compromised skin barrier [23].

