### Statistical analysis plan

Hypothesis testing for this study will be based on a superiority framework and will be conducted at the α = 0.05 significance level. Primary analyses will be conducted using a complete-case, intention-to-treat approach, where participants will be analyzed in the trial arm their cluster was randomized to, irrespective of contamination or adherence to instructions on how to use the iNCK. The unit of analysis will be the individual neonate (neonatal mortality, omphalitis, fever, hypothermia, and healthcare utilization for newborn morbidities) or the individual woman (PPH and healthcare utilization for PPH). Risk ratios for the primary (neonatal mortality) and secondary (omphalitis and PPH) outcomes will be estimated using multivariable modified Poisson regression [29], with generalized estimating equations to account for the clustered design and robust variance estimators to account for multiple births and/or multiple pregnancies during the study period. Analyses of neonatal mortality (the primary outcome) will adjust for newborn sex, antenatal care, and gestational age at birth to improve power and efficiency; calendar time to account for underlying temporal trends (defined as month of birth, setting month of study launch as month 0); and the covariates used in the randomization procedure: GB study district, log cluster-specific baseline NMRs, and the cluster-specific baseline proportion of children delivered at a health facility. Analyses of omphalitis (secondary outcome) will adjust for newborn sex, antenatal care, and GB study district. Analyses of PPH (secondary outcome) will exclude women who delivered via C-section, and will adjust for parity, maternal age, history of prior C-section, history of prior PPH, GB study district, and the cluster-specific baseline proportion of women who reported experiencing PPH. The frequency of hypothermia, cold stress, and fever detected by ThermoSpot™ within the first 14 days of life will be described amongst participants in intervention clusters only, overall and by calendar month to assess seasonality. Finally, the frequency and location of health facility utilization for omphalitis, PPH, hypothermia, and fever will be described using counts and proportions amongst individuals experiencing each respective morbidity and will be stratified by trial arm. The proportion accessing healthcare services by trial arm will be compared using clustered t-tests and modified Poisson regression.

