Subgroup analyses will examine primary and secondary outcomes by place of delivery, GB district, newborn sex, gestational age at birth, the timing of intervention delivery relative to the date of birth, and the frequency of postnatal LHW home visits (Table 2). For analyses of neonatal mortality, omphalitis, and PPH, interaction terms between trial arm and each subgroup or process indicator will be analyzed in separate models. We will also describe compliance to the iNCK package and its components among intervention arm participants, including overall uptake as well as the timing and duration of usage. In secondary, per-protocol analyses of the primary and secondary outcomes, intervention arm participants will be assigned compliance scores using an algorithm defined in Supplemental Tables 1 and 2. Participants scoring at or above thresholds of compliance (e.g., 60%, 70%, 80%, 90%, and 100%) will be propensity-score matched to participants in control clusters, and modified Poisson regression will be used as above to compare good compliers with their matched unexposed participants. Finally, we will conduct supplementary analyses of the primary neonatal mortality outcome using alternative mortality definitions (i.e., death on day 1, days 1–7, days 8–28, days 2–7, and days 2–28).

Cause of death will be ascertained using VA data using previously described methods and will also inform the primary analysis by differentiating stillbirths from early neonatal deaths [30]. Stata version 17.0 or newer will be used for all analyses.

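### For PPH, the planned interaction with postnatal LHW visits uses a factor that follows the kit's action and may respond to the bleed; the per-protocol PPH comparison shares the problem if its score counts later newborn care

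*Protocol article*

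**What the plan says.** All analysis statements below are in the protocol article, Statistical analysis plan section.

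- The subgroup factors include "the timing of intervention delivery relative to the date of birth, and the frequency of postnatal LHW home visits". They are applied to PPH by name: "For analyses of neonatal mortality, omphalitis, and PPH, interaction terms between trial arm and each subgroup or process indicator will be analyzed in separate models".
- On compliance: "In secondary, per-protocol analyses of the primary and secondary outcomes, intervention arm participants will be assigned compliance scores". The scoring rule itself is not in the article's text; it refers the reader elsewhere for it, with scores produced "using an algorithm defined in Supplemental Tables 1 and 2". Women at or above a threshold (examples from 60% to 100%) are then propensity-score matched to control-arm participants, who carry no score. PPH is a secondary outcome, so this covers it.
- The main PPH analysis is by intention to treat. "Analyses of PPH (secondary outcome) will exclude women who delivered via C-section". Testing "will be conducted at the α = 0.05 significance level".

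On timing, the Misoprostol section has mothers "take the three tablets immediately after delivery of the baby and before delivery of the placenta". Other components run much longer: the emollient is used "once per day, from the day of birth until day 28 of life", chlorhexidine to day 10 and ThermoSpot to day 14. Table 2 lists PPH as a cumulative incidence without a time window. Only LHWs in intervention clusters received scales, for weighing the newborn at their first visit after the birth.

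**The concern.** An effect modifier should be fixed before the outcome it is meant to modify. Misoprostol is the only component the article describes as preventing PPH, and it is used once, at delivery. Visits made afterwards cannot alter what the tablets did. A bleed, however, can alter the visits: the woman may be ill, referred, away from home or followed more closely. Grouping women by visit count may therefore group them partly by the outcome.

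The per-protocol comparison raises a related question. If the score for PPH includes newborn care given after the bleed, PPH can move intervention women into or out of the complier group while the matched controls keep all their PPH cases. A propensity score built on baseline characteristics cannot balance selection that the outcome itself caused.

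At stake is whether a difference by visit intensity or by compliance is reported as evidence about the kit when it reflects only this sorting.

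**Working it through.** The article gives no figure to reproduce on this point. It does not state the PPH risk, the PPH intracluster correlation (ICC), or how visits and compliance vary with PPH. All such values below are assumptions. Throughout, the kit has no effect: PPH risk p is the same in both arms, with p = 0.10 unless stated.

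**Visit interaction.** Within an arm, let a1 and a0 be the probabilities of being frequently visited with and without PPH.

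- Risk among the frequently visited = p·a1 / [p·a1 + (1−p)·a0]
- Risk among the infrequently visited = p(1−a1) / [p(1−a1) + (1−p)(1−a0)]

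Control arm in scenarios 1 to 3: a0 = 0.50, a1 = 0.70. The risks are 0.07/0.52 = 0.135 (frequent) and 0.03/0.48 = 0.0625 (infrequent).

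1. Intervention arm identical (0.50, 0.70): risk ratios (RRs) 1.00 and 1.00. No bias, although PPH does change visiting.
2. Intervention arm visited more throughout (0.70, 0.90): 0.09/0.72 = 0.125, RR 0.93; 0.01/0.28 = 0.0357, RR 0.57. Interaction ratio 0.929/0.571 = 1.63.
3. Intervention arm visited more only when there is no PPH (0.65, 0.70): 0.07/0.655 = 0.107, RR 0.79; 0.03/0.345 = 0.0870, RR 1.39. Ratio 0.794/1.391 = 0.57.
4. Intervention arm visited more (0.70 against 0.50) but visits unrelated to PPH in either arm: RRs 1.00 and 1.00.

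A false interaction therefore needs two things together: visits that respond to PPH, and a difference between arms in visiting or in that response. The ratios 0.57 and 1.63 are illustrations, not bounds. If PPH raised visiting only in the intervention arm (0.50 to 0.70, controls 0.50 throughout), the ratio would be (0.1346/0.10)/(0.0625/0.10) = 2.15.

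**Per-protocol comparison, if the score counts care after the bleed.** Let c1 and c0 be the probabilities of reaching the threshold with and without PPH. Controls are unscored, so their risk stays p, and

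null RR = c1 / [p·c1 + (1−p)·c0].

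With c0 = 0.50:

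- c1 = 0.50: RR 1.00
- c1 = 0.40 (20% less likely): 0.40/0.49 = 0.82
- c1 = 0.60 (20% more likely): 0.60/0.51 = 1.18

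Over p from 5% to 20%, the last two become 0.81 to 0.83 and 1.15 to 1.19.

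**What an RR of 0.82 would do to the test.** The Sample size section plans 39 clusters per arm and 306 births per cluster, so 39 × 306 = 11,934. The complier share is 0.10 × 0.40 + 0.90 × 0.50 = 0.49, giving about 5,848 compliers, taken as matched 1:1. The comparison is 8.16% against 10%. The design effect is 1 + (5,848/39 − 1) × ICC, which is 1.30, 2.49 and 3.98 at assumed PPH ICCs of 0.002, 0.01 and 0.02. At a two-sided 5% level (sidedness assumed), a true null would be rejected 86%, 59% and 41% of the time. This ignores the exclusion of C-section deliveries and counts births as women.

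**The case against.** The strongest reply is that much of this depends on facts not shown, and most of that reply stands.

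- **The score.** A reader might infer that women are scored for PPH on emollient, cord care and ThermoSpot use. The article does not say so. The algorithm is in Supplemental Tables 1 and 2, and the article also describes compliance by component, so an outcome-specific score is possible. Percentage thresholds from 60% to 100% suggest several components, but that is inference.
- **The direction.** A reader might infer that women who bleed necessarily fall out of the complier group. Chlorhexidine and emollient may be applied by the mother or another caregiver, and family members present are also instructed, so newborn care need not suffer. If compliance does not depend on PPH, this distortion is absent.
- **The visits.** A reader might infer that PPH sorting women by visit count is enough to cause bias. Scenario 1 shows it is not. LHWs in both arms share a monthly household-visit mandate. The weighing task makes an arm difference plausible, but it concerns the newborn and is not shown to change visit numbers or the response to a bleed.
- **The PPH window.** None is stated, so a late bleed could follow some visits. A visit count not limited to the time before the bleed would still mix visits before and after it.
- **Omphalitis.** It is tempting to extend the criticism to care given after onset. A remedy there would need onset dates, which the article does not show are collected, so the extension is not pressed.

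What the reply does not meet is that the visit interaction is specified for PPH by name. Nothing in the article limits it to visits before the bleed, and further analysis detail would not make a later visit a modifier of an effect already complete.

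**Conclusion.** The point holds in a limited form. The PPH interaction with postnatal visit frequency is explicit and poorly chosen: it cannot show modification of the misoprostol effect, and it can show a false one. The size is conditional: ratios of about 0.57 and 1.63 in two assumed scenarios at 10% PPH risk, and none if visiting is identical in both arms or unrelated to PPH.

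The per-protocol part is conditional on the supplement. If the PPH score counts care after the bleed, the null RR is about 0.82 or 1.18 for a 20% lower or higher chance of reaching the threshold. If it rests on misoprostol alone, the path through later newborn care is closed, though ordinary confounding between compliers and matched controls may remain.

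A reader might infer that the trial's PPH finding is compromised. It is not: the main PPH analysis is by intention to treat and uses neither grouping. The change is worth making because it costs little, but the affected analyses are subgroup and secondary ones.

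**What to change.** 1. For PPH, remove postnatal visit frequency from the interaction models, or tabulate it by arm and state that it is descriptive and not evidence of effect modification.
2. For the per-protocol PPH analysis, define compliance by the misoprostol item alone, counted as used at the instructed time, or confirm that Supplemental Tables 1 and 2 already do this. Use that began in response to bleeding should not count, because it too would follow the outcome.
3. Optionally, add a complier effect from the randomised contrast as a sensitivity analysis: the intention-to-treat risk difference divided by the proportion of intervention women who took the tablets. State its assumptions: the kit affects PPH only through the tablets, and controls do not take them. The first needs defending here, because the trial is open-label and outcomes are collected by interview, so kit education could affect reporting.

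The cost of items 1 and 2 is one interaction test fewer and a change of wording. No new data should be needed: the diary is meant to record whether and when components were used, and unused tablets are retrieved at the day 29 visit. Item 3 would give a wider interval than the matched comparison.

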**Fig. 1 Fig1:**
[figure not shown]
Contents of the iNCK, which includes: **A** Clean birth kit: Ai) Clean plastic sheet, Aii) surgical gloves, Aiii) maternity pad, Aiv) cotton balls, Av) cord clamp, Avi) antibacterial soap bar, **B** chlorhexidine 4% gel **C** three 200 μg misoprostol tablets, **D** sunflower oil emollient, **E** ThermoSpot™ sticker, **F** Click-to-heat warmer, **G** fleece blanket, **H** pictorial diary for documenting use of iNCK components, **I** pictorial guide, **J** battery-operated weighing scale (used by LHW)

**Table 1 Tab1:** Description of each iNCK component and its intended use

Kit content	Description and intended use
Clean birth kit (CBK)	**•**Sterile blade to cut the umbilical cord **•**Clean plastic sheet to be placed on the ground or **•**surface for birth **•**Plastic gloves to be worn by the birth attendant **•**Hand soap **•**Two cord clamps **•**Maternity pad to absorb peri- and post-natal bleeding **•**Ten cotton balls to apply CHX
Chlorhexidine (CHX)	**•**10 gm of 4% CHX topical gel, a broad-spectrum antiseptic, in a small plastic tube. CHX should be applied once per day from the first day of the baby’s life until day 10 of life
Misoprostol	**•**Three 200 µg dissolvable misoprostol tablets to be used prophylactically to prevent PPH. The tablets should be taken immediately after delivery of the baby and before delivery of the placenta. For participants who deliver via C-section, the attending clinician will decide whether or not to administer misoprostol
Sunflower oil emollient	**•**50 ml of sunflower oil emollient packaged in a small plastic bottle to massage over the newborn’s skin, avoiding the face and scalp. Sunflower oil emollient should be applied once per day from the first day of the baby's life until day 28 of life
ThermoSpot ™	**•**12 mm diameter round sticker that adheres to the skin and changes color based on body temperature. ThermoSpot™ should be applied to the baby’s neck over the carotid artery on the first day of the baby's life and left in place until day 14 of life
Fleece blanket	**•**One fleece blanket (65 × 86 cm), to wrap the baby along with the activated warmer whenever moderate to severe hypothermia is detected by ThermoSpot™

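### The per-protocol mortality analysis selects kit-arm compliers on a score that builds up during the 28-day outcome window, which can bias it towards benefit; the postnatal-visit subgroup also depends on survival

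*Protocol article*

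**What the plan says.** The Statistical analysis plan section of the protocol article introduces the analysis with "In secondary, per-protocol analyses of the primary and secondary outcomes". It then states that "intervention arm participants will be assigned compliance scores using an algorithm defined in Supplemental Tables 1 and 2", and that "Participants scoring at or above thresholds of compliance (e.g., 60%, 70%, 80%, 90%, and 100%) will be propensity-score matched to participants in control clusters". Modified Poisson regression compares the two matched groups. The section states no landmark and no survival requirement for the controls.

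Table 1 gives the schedules that compliance would be judged against. For chlorhexidine: "CHX should be applied once per day from the first day of the baby’s life until day 10 of life". For the emollient: "Sunflower oil emollient should be applied once per day from the first day of the baby's life until day 28 of life". The ThermoSpot sticker stays on until day 14. The clean birth kit and misoprostol are used at delivery. The primary outcome (Study outcome measures) is death within the first 28 days.

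The subgroup list in the same section includes "the timing of intervention delivery relative to the date of birth, and the frequency of postnatal LHW home visits". For mortality, each subgroup variable enters a separate model as an interaction with trial arm, so visit frequency stratifies both arms.

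The primary analysis is intention-to-treat, regardless of adherence.

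**The concern.** A newborn can build up days of use only while alive. If the score counts those days, passing a threshold partly means having survived, and this filter is applied in the kit arm alone. The matched controls keep all their early deaths. This is immortal-time bias. Propensity matching on baseline covariates cannot repair it, because survival after birth is not a baseline covariate.

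The pilot described under Rationale found no significant mortality difference (risk ratio 0.83, 95% CI 0.58 to 1.18) and poor adherence to instructions. If this trial's intention-to-treat result were also inconclusive, readers would naturally turn to the estimate among good compliers, and a biased one could be read as proof that the kit works when used properly.

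Visit frequency has a related weakness. Newborns who die early have had less time to be visited, so the count is partly a consequence of the outcome.

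**Working it through.** The protocol gives no figure for these analyses, so there is none to reproduce. The checks below ask what they would show if the kit did nothing.

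**Inputs from the protocol.** Neonatal mortality 35 per 1,000 and design risk ratio 0.75 (Sample size); schedules of 10, 14 and 28 days (Table 1); thresholds from 60% to 100%; day-1 starting in the pilot of 32% for chlorhexidine and 28% for ThermoSpot among users (Rationale).

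**Assumptions.** Share of neonatal deaths on day 1 / days 2–7 / days 8–28: 35/40/25 (central), 25/25/50 and 50/30/20. Five equally weighted components: birth kit, misoprostol, chlorhexidine, emollient, ThermoSpot. Adherence is unrelated to the risk of death, so comparing with all controls is equivalent to comparing with matched ones.

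**1. Highest possible score by day of death D, full-schedule scoring**

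Score = [2 + min(D,10)/10 + min(D,14)/14 + D/28] / 5. On day 7: (2 + 0.70 + 0.50 + 0.25)/5 = 0.69. For the three daily components alone, drop the 2 and divide by 3.

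| Death on day | Five components | Three daily components |
|---|---|---|
| 1 | 44% | 7% |
| 3 | 52% | 21% |
| 7 | 69% | 48% |
| 10 | 81% | 69% |
| 14 | 90% | 83% |

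A score of 100% requires survival to day 28.

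**2. Hand check at the 60% threshold, perfect adherence**

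The five-component ceiling is 57% on day 4 and 61% on day 5, so deaths on days 1–4 cannot qualify. Under the central timing these are 35% + 40% × 3/6 = 55% of deaths. Null risk ratio = 0.45 / (1 − 0.035 × 0.55) = 0.46. The other two timings give 0.625 / (1 − 0.035 × 0.375) = 0.63 and 0.35 / (1 − 0.035 × 0.65) = 0.36.

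**3. Simulation with imperfect adherence, full-schedule scoring**

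Daily use probability averaged 75%, birth-kit use 90% and misoprostol use 85%, with everyone starting on day 1. Ranges are over the three timings.

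| Threshold | Null risk ratio |
|---|---|
| 60% | 0.24–0.51 |
| 70% | 0.17–0.42 |
| 80% | 0.13–0.33 |
| 90% | 0.07–0.18 |

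Varying the start-day assumptions widens the 60% range to about 0.2–0.55.

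**4. Days-alive scoring**

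- Everyone starts on day 1: 0.97–1.22. There is no protective artefact; at 80–90% it leans the other way, because a short life makes a high proportion easier to reach.
- Day-1 starting near the pilot rates (30% assumed for emollient), late starts on days 2–4, 90% daily use afterwards: about 0.3–0.85 across the 60–90% thresholds if lateness is independent by component, and 0.54–0.77 if the same caregivers are late throughout. A late starter whose baby dies on day 1 scores nothing on the daily items; the same caregiver with a surviving baby can pass.
- About 90% starting on day 1: close to 1 at most thresholds.

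**5. Visit subgroup**

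Visits accrue at random while the newborn is alive, 1.5 per 28 days in controls (assumed), central death timing. With equal rates, mortality is 10.8%, 1.9% and 0.6% at 0, 1 and 2 or more visits in both arms, so the count reflects survival. Null risk ratios between arms:

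| Kit-arm visits per 28 days | 0 visits | 1 visit | 2 or more |
|---|---|---|---|
| 1.5 | 1.00 | 0.99 | 1.01 |
| 2.0 | 1.45 | 1.37 | 1.09 |
| 1.0 | 0.68 | 0.75 | 0.95 |

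**The case against.** The strongest objection is that the scoring algorithm sits in Supplemental Tables 1 and 2, which are not shown. A score based on starting on day 1 gave a null risk ratio of 1.00–1.01, and days-alive scoring with universal day-1 starting gave no protective artefact. The phrase "including overall uptake as well as the timing and duration of usage" belongs to the descriptive compliance summary and is not stated to be part of the score. This stands against saying that the analysis will be biased. It does not clear the plan: days-alive scoring stays biased when first use is delayed, as it was in the pilot. The new pictorial guide may improve early starting, but that is one of the trial's open questions.

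Four stronger readings are tempting and not supported:

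- *A newborn dying in the first week cannot reach 60%.* With the birth kit and misoprostol counted, a death on day 7 can still score 69%.
- *The visit subgroup also makes the kit look protective.* Both arms are stratified, so equal visit rates give no between-arm bias, and more kit-arm visits make the kit look harmful within strata. Only intervention LHWs received scales, but weighing takes place at the first post-delivery visit and the protocol describes no additional visit, so the direction of any difference is unknown.
- *All per-protocol outcomes are affected alike.* The mechanism is newborn death; it does not carry over in the same way to postpartum haemorrhage, where misoprostol is taken at delivery.
- *The trial's main conclusion is at risk.* These are secondary analyses, and intention-to-treat is primary.

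**Conclusion.** The concern holds in conditional form. As described, the per-protocol mortality contrast applies a filter that can depend on survival to one arm only, and it can show benefit from an inert kit unless the score is confined to actions at birth or on day 1. Under full-schedule scoring the illustrative artefact at the 60% threshold (about 0.2–0.55 with imperfect adherence, 0.36–0.63 with perfect adherence) is larger than the design effect of 0.75. Under days-alive scoring it ranges from severe to negligible, depending on the timing of first use. Death timing, adherence, component weights and start days are all assumed, so these figures show scale and are not predictions.

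Visit frequency should not be read as an effect modifier for mortality. If the kit arm is visited more, the kit looks harmful within strata, with a false trend towards a better effect at more visits; if it is visited less, the pattern reverses.

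Severity is moderate: secondary analyses only.

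**What to change.** 1. For mortality, define per-protocol exposure by what can be done at birth or on day 1 (birth kit used, chlorhexidine and ThermoSpot started). Set a landmark at the end of that window. In both arms, include only newborns alive at the landmark and count only deaths after it. Keep the propensity matching for measured baseline differences.
2. Report the longer-duration compliance scores and the 60–100% thresholds descriptively for mortality. If the supplementary tables already restrict the score to birth or day 1, say so in the analysis plan and add the common landmark.
3. Replace visit frequency as a mortality effect modifier with a pre-birth or cluster-level measure, such as LHW coverage from the baseline survey, or describe it only.

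The cost is a change of wording in the analysis plan, with no new data collection. The drawback is that deaths before the landmark do not contribute to the per-protocol estimate, including any that the birth kit might have prevented. The intention-to-treat analysis keeps them.
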